# Promoting Alcohol Reduction in Non-Treatment Seeking parents (PAReNTS): a protocol for a pilot feasibility cluster randomised controlled trial of alcohol screening and brief interventions to reduce parental alcohol use disorders in vulnerable families

**DOI:** 10.1186/s40814-018-0305-5

**Published:** 2018-06-09

**Keywords:** Alcohol, Brief interventions, Parent, Vulnerable families, Children’s social care

## Abstract

**Background:**

Research estimates that 30% of children under the age of 16 years in the UK live with at least one parent with an alcohol use disorder (AUD). Parental AUDs are associated with adverse childhood experiences and poorer outcomes for children. The PAReNTS (Promoting Alcohol Reduction in Non-Treatment Seeking parents) trial aims to examine the feasibility and acceptability of a randomised controlled trial of brief alcohol interventions to reduce parental alcohol misuse.

**Methods:**

The cluster randomised controlled trial will be conducted within early help family support and children’s social care services in three local authorities in the North East of England: Newcastle, Durham and North Tyneside. All eligible parents the caseloads of participating practitioners will be screened for an AUD using the Alcohol Use Disorder Identification Test – Consumption (AUDIT-C) screening tool by the social care practitioners within routine appointments. All parents who score 5 or more on the AUDIT-C will be invited to participate in the trial. Consenting participants will complete a baseline questionnaire before receiving one of three randomised interventions: (i) healthy lifestyle leaflet (control intervention); (ii) a brief alcohol advice intervention delivered by the social care practitioner plus healthy lifestyle leaflet; (iii) a brief alcohol advice intervention delivered by the social care practitioner, healthy lifestyle leaflet plus a 40-min behaviour change intervention with an optional review session delivered by the local alcohol service. Follow-up data will be collected 6 and 12 months post recruitment. A linked qualitative study will explore participating parent and practitioner views on the acceptability of trial processes and interventions.

**Discussion:**

The PAReNTS trial will provide a robust estimate of recruitment, retention and consent rates in order to inform the design of a future definitive study examining the effectiveness and cost-effectiveness of alcohol screening and brief interventions to reduce parental AUDs within vulnerable families.

**Trial registration:**

ISRCTN registry ISRCTN60291091; protocol version 2; 17.10.2016

**Electronic supplementary material:**

The online version of this article (10.1186/s40814-018-0305-5) contains supplementary material, which is available to authorized users.

## Background

Approximately 30% (3.3–3.5 million) of children under 16 years of age [1] and 12% (93,517) of infants under 1 year of age [2] in the UK live with a parent who has an alcohol use disorder (AUD). There are three categories of AUD: hazardous, harmful and dependent drinking. Hazardous drinking is a repeated pattern of drinking that increases the risk of physical or psychological problems whilst harmful drinking is defined by the presence of these problems [3]. Alcohol dependence is defined as a cluster of physiological, behavioural and cognitive phenomena in which the use of alcohol takes on much higher priority for a given individual than other behaviours that once had greater value [3]. There is well-established evidence documenting the harmful effect that parental alcohol dependency has upon the child throughout their life course [4]. Children whose parents are dependent upon alcohol are more likely to suffer an injury [5], as well as an injury of greater severity [6], and to experience health problems to which their parents may not respond effectively [4]. Pre-school children are at risk of delays in cognitive and language development [7] and a greater likelihood of education deficits [8]. They can go on to have lower educational performance in adolescence [9], resulting in poor life chances [4]. However, the association between parental alcohol misuse and adverse outcomes in children is not restricted to dependent levels of use [10]. Parental AUD below dependent levels is also associated with childhood accidental injury [11, 12], hospital admissions [13], externalising difficulties [14–16] and lower school performance [17]. Children whose parents display non-dependent AUD are themselves likely to go on to early onset alcohol use [18], regular alcohol consumption [19] and alcohol intoxication [20].

Due to the potential negative impact on the child, parental AUDs are emphasised as a parental risk factor within guidance on safeguarding children [21]. In England, parental alcohol misuse was identified as a risk factor in 19% of child in need assessments [22]. A study of cases allocated for a long-term social work intervention found that parental ‘alcohol misuse’ (non-defined) was a concern in 68 out of the 290 cases (23%) [23]. Fifty-six percent of mothers who have been involved in recurrent care proceedings were engaged in misuse of alcohol and others drugs during the index proceedings [24]. Moreover, parental alcohol misuse was recorded in 37% of serious case reviews (local enquiry following the death or serious harm to a child where abuse or neglect are known or suspected) [25]. Whilst practitioners within children’s social care consider it a legitimate part of their role to ask parents about their alcohol use, they experience difficulty in identifying parents who have AUDs [26, 27]. Practitioners typically rely upon observations of parental intoxication or informal assessment of alcohol problems. Such methods are unlikely to identify parental AUDs below the diagnostic threshold for dependence, resulting in a dichotomous assessment of the presence or absence of alcohol problems, rather than recognition of a continuum of risk. Indeed, the lack of valid alcohol and other drug use assessment tools within social care settings has been highlighted in research [26]. Furthermore, those parents that are identified as misusing alcohol often do not receive an intervention, with parents expressing reluctance to engage with specialist drug and alcohol treatment providers as they did not perceive themselves as having a substance misuse problem [23]. Given the propensity of harms to children associated with parental alcohol misuse, as well as the harms to the individual drinker, it is both a public health [28] and safeguarding priority [29] to address parental AUDs. In a major review of UK child protection services, preventive rather than reactive services were highlighted to be more effective in reducing abuse and neglect of children [30]. The importance of intervening early in parental AUDs amongst other parental stressors has been highlighted in guidance for health, social care and third sector partners [21, 30, 31], yet recent inspections have found that services do not sufficiently recognise the needs of families affected by parental alcohol misuse [32, 33].

A number of trials have examined the effectiveness of psychological interventions in reducing parental alcohol and drug misuse. Whilst the findings of these trials are mixed, there is some evidence that interventions with a focus upon the family or those with clear extrinsic motivation for the parent (such as those linked to care proceedings) are effective at reducing parental alcohol and drug misuse. Statistically significant reductions in parental substance use were found in interventions which included parental skill training and education [34–37], those that were ecological or systemic in their approach [38, 39] and those that involved relational therapy [36, 40]. However, much of this research was reactive, focused upon parents who were dependent upon alcohol or other drugs and whose use of substances were directly related to incidents of child abuse and neglect.

There is a paucity of research on preventive interventions to reduce AUD in parents [41]. There is, however, a large amount of high-quality evidence to support the effectiveness of alcohol screening and brief interventions with adults who have AUDs [42]. Indeed, the evidence base for brief interventions represents the largest, most robust body of evidence for alcohol interventions [43]. Most of this evidence base has been developed in primary care, however; other settings have learned from these studies and examined the benefits to their patients. Indeed, there have been a number of systematic reviews and individual studies of brief interventions in emergency departments [44, 45] and with other populations such as young people [46, 47] and pregnant women [48, 49] showing some beneficial effect. However, there are no studies examining the effectiveness of alcohol screening and brief interventions within social care settings or brief interventions delivered to parent populations.

## Aim

The PAReNTS (Promoting Alcohol Reduction in Non-Treatment Seeking parents) study is a pilot feasibility randomised controlled trial of brief alcohol interventions to reduce parental AUD. The trial aims to investigate whether it is possible to recruit parents involved with early help family support (voluntary support) or children’s social care (statutory intervention) who have an AUD, and whether these parents can be retained at the 12-month follow-up. The feasibility and acceptability of the study interventions and trial procedures will be examined. If feasibility and acceptability is shown, the pilot feasibility trial will inform the protocol for a definitive cluster randomised controlled trial.

The specific objectives of this pilot feasibility trial are:To assess local authority engagement in an alcohol trial that uses a randomised controlled designTo estimate rates of participant eligibility, recruitment, randomisation, retention and response to outcome measures within the baseline and follow-up questionnaires to inform sample size calculations for a future definitive trialTo assess engagement and participation with the alcohol interventionsTo develop cost assessment tools, assess intervention delivery costs and carry out a value of information analysis to inform a definitive trialTo apply pre-specified ‘stop/go’ criteria to determine if a definitive multi-centre randomised controlled trial is feasible and, if so, to develop a full trial protocol.

A clear success criteria (‘go’) would be meeting of all of the targets of recruitment of three local authorities as research sites from within the North East region of England; ≥ 60% of eligible participants consenting to pilot feasibility trial; ≥ 60% of consenting participants accepting/attending intervention sessions; retention of ≥ 60% of consented participants for provision of key outcome data at 12 months. These are common parameters considered when decided upon progression to definitive trial [50]. Whilst within randomised controlled trials of brief alcohol interventions in primary care settings often report a consent rate of 80% and aim to retain 70% of participants at the 12-month follow-up [51], parents involved in early help family support and children’s social care are a vulnerable population and external factors within their daily living may reduce the likelihood of providing consent to participate in the trial and of being retained at follow-up. As such, more cautious success criteria have been suggested. Receipt of interventions delivered opportunistically is typically high in trials of brief interventions (99%); however, attendance at scheduled brief interventions wherein a participant is required to return at a later date for an appointment is much lower (around 50–60%) [51–53]. To allow for this variation between interventions, the intervention will be considered to have met the success criteria if ≥ 60% of randomised participants in each arm receive the intervention. Where marginal results are reached (recruitment of two local authorities; 59–40% of eligible participants consenting to pilot feasibility trial; retention of 59–50% of consented participants at 12 months; 59–30% of participants receiving a randomised intervention), a process for decision making after pilot and feasibility trials (ADePT) [54] will be followed, systematically appraising the problems and potential solutions within the linked process evaluation.

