## Methods

### Recruitment and screening

The trial will be conducted within early help family support and children’s social care services in three local authorities in the North East of England: Newcastle, Durham and North Tyneside. These particular local authorities were selected due to their geographical and service model variability. Participating practitioners within early help family support and children’s social care services will screen all eligible parents on their caseloads for AUDs within routine appointments. To be eligible, parents must be 18 years or over and be able to give informed consent in English. A broad definition of ‘parent’ will be applied wherein any adult who fulfils a parenting role (as identified by the additional early help family support and/or children’s social care assessment) for a child aged 0–17 years will be considered eligible for the study. This includes both mothers and fathers, step parents and other caregivers. Parents who are attending drug and alcohol services; who have severe, chronic or acute mental health problems or are severely distressed; or whose child is placed on an emergency protection order will be ineligible to participate in the study. Social care practitioners will record demographics of all eligible parents and provide details of the reason for social care involvement. The social care practitioner will administer the Alcohol Use Disorder Identification Test – Consumption (AUDIT-C) screening tool, which measures alcohol consumption [55]. The AUDIT-C is a three-item tool that has been found to have comparable sensitivity to the 10-item AUDIT in detecting heavy drinking; it performs better than the 10-item AUDIT in detecting alcohol dependence in women and has greater efficiency in screening hazardous alcohol use in men [56]. The tool was considered to be preferable to the 10-item version for use in early help family support and children’s social care setting. Parents within this setting are likely to be concerned that their parenting capacity will be negatively judged and may therefore be reluctant to provide an accurate response to the dependence and control items of the 10-item AUDIT. Moreover, the use of the AUDIT-C is in-line with usual practice in social care. It has been validated using a cut-off score of ≥ 5 in European general populations [57], men and middle-aged women [58]. Those parents screening positive for AUD on the AUDIT-C (an AUDIT score of ≥ 5) [59] will be invited to participate in the trial by the social care practitioner. The social care practitioner will provide a participant information leaflet to the parent, explain the trial and seek informed written consent for participation. In families where multiple caregivers screen positive and agree to participate, the parents will be recruited as individual cases.

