### Consent

Social care practitioners will provide all parents on their caseloads with an information leaflet about the study a minimum of 24 h in advance of conducting alcohol screening. After administering the AUDIT-C, social care practitioners will explain the study to eligible parents who screen positive for an AUD and answer any questions they may have. If the parent decides to participate, they will be asked to provide written consent, which will be recorded on a consent form (please see consent form in the Additional file 1: Appendix). Additional consent will also be sought for qualitative interviews which will be conducted within the process evaluation, and audio-recording of intervention sessions (to enable fidelity assessments). The consent form will include a unique identifier which enables the consent to be linked to the anonymised personal data gathered within the baseline questionnaire.

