### Training and fidelity

The unit of randomisation within this cluster randomised controlled trial will be the social care practitioner. Practitioners will only be trained in the intervention to which they are randomised, with practitioners in the control group receiving no intervention training. This approach will restrict their knowledge of the skills and techniques used in other intervention groups and is therefore expected to reduce the likelihood of contamination between groups. Within each local authority area, a specialist alcohol treatment provider will be recruited to deliver the extended alcohol intervention. All social care practitioners will be trained in general trial procedures and their own randomised intervention. This training for the control group will last 1 h and will focus on the aims of the trial, trial procedures and issuing the healthy lifestyle leaflet. The training for the social care practitioners within both the brief alcohol advice and extended alcohol intervention groups will last around 4 h and will cover the impact of parental alcohol misuse upon children, the aims of the trial, trial procedures and delivery of the brief alcohol advice intervention. Practitioners within the extended alcohol intervention group will also receive information on the process for referring participants to the alcohol treatment service and the content of the extended alcohol intervention. Specialist alcohol practitioners will be trained to deliver the extended alcohol intervention. This training will last around 2 h and will cover the aims of the trial and delivery of the extended intervention.

Twenty percent of the brief and extended alcohol interventions (*n* = 12 of each intervention) will be audio-recorded and assessed for intervention fidelity. We will apply an a priori designed checklist tool to assess the fidelity of intervention delivery of the brief intervention sessions. We will assess the extended intervention using a validated rating scale (BECCI) [72].

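### The consent progression criterion leaves its denominator unclear (23% or 78% from the same planned data), and no criterion depends on how many parents are screened or recruited

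*Protocol article*

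**What the plan says.** One objective in the Aim section is to apply pre-specified stop/go criteria. A clear *go* needs all of these:

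- three local authorities recruited;
- at least 60% "of eligible participants consenting to pilot feasibility trial";
- at least 60% of participants receiving the intervention, to be met in each arm;
- at least 60% of consented participants retained for key outcome data at 12 months.

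The marginal band for consent is "59–40% of eligible participants consenting to pilot feasibility trial". Marginal results go to a structured appraisal (ADePT).

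Recruitment and screening defines eligibility without the AUDIT-C: "To be eligible, parents must be 18 years or over and be able to give informed consent in English", together with a parenting role and several exclusions. Practitioners then "will screen all eligible parents on their caseloads for AUDs within routine appointments". Parents scoring 5 or more "will be invited to participate in the trial by the social care practitioner". The Consent section keeps the two steps apart: "social care practitioners will explain the study to eligible parents who screen positive for an AUD".

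The Aim section says that the trial investigates "whether it is possible to recruit parents involved with early help family support" and children's social care. Sample size asks for at least 35 respondents per arm at 12 months and for 60 recruits per arm. Training and fidelity states: "Practitioners will only be trained in the intervention to which they are randomised".

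**The concern.** The progression decision is a main output of a pilot trial, so the rule must give one answer from one set of data. The key word in the consent criterion, *eligible*, has a meaning elsewhere in the protocol that makes the criterion unreachable under the planning assumptions. The meaning that makes it workable is not written down. A pre-specified rule should not leave that choice until the data are in.

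The workable meaning leaves a second gap. The Discussion names reluctance to disclose drinking and busy practitioners as risks. Both act before consent is sought, by cutting the number screened or the number screening positive. A consent ratio among invited parents does not register either of them, and no other criterion does.

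Third, practitioners are randomised and trained for their own arm, and they themselves screen and seek consent. The arms could therefore differ in who screens positive and who consents. This matters for the definitive cluster trial, and the stated consent criterion has no by-arm element.

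**Working it through.** **Inputs.** From Sample size: 921 parents approached, 84% meeting the inclusion criteria, 30% scoring 5 or more on the AUDIT-C, 78% consenting, 60 recruits per arm (180 in all), 42% loss, 35 respondents per arm. From Aim: the 60% and 40% thresholds.

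**1. Reproduce the plan's funnel.**
- Eligible: 921 × 0.84 = 773.6
- Screen-positive: 773.6 × 0.30 = 232.1
- Consenting: 232.1 × 0.78 = 181.0, against the 180 planned

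The funnel reproduces. The fault is in the criterion, not in the sample-size arithmetic.

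**2. Apply the consent criterion under each reading.**

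| Denominator | Expected at plan | Maximum (all screen-positives consent) | Result at plan |
|---|---|---|---|
| Eligible, before AUDIT-C (774) | 181/774 = 23.4% | 232/774 = 30% | below the 40% marginal floor |
| Eligible, screen-positive and invited (232) | 181/232 = 78% | 100% | *go* |

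On the first reading, 60% would need 0.60 × 774 = 464 consents. That means 60% positivity with every positive parent consenting, or 0.60/0.78 = 77% positivity at 78% consent. The marginal floor would need 0.40/0.78 = 51% positivity at 78% consent.

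**3. Test the intended reading for volume.** Suppose practitioners reach one tenth of plan: 92.1 × 0.84 = 77.4 eligible, × 0.30 = 23.2 positive, × 0.78 = 18.1 consenting.
- Consent: 18/23 = 78%, *go*
- Retention, if 11 of 18 respond: 61%, *go*
- Receipt, if 4 of 6 per arm: 67%, *go*
- Recruits: 18/180 = 10% of target
- Respondents: 11/3 = about 4 per arm, against 35

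With the three authorities in place, every criterion is met.

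A ratio from few parents is also weak evidence. If true consent were 50%, the binomial chance of observing 60% or more is 38% with 10 invited parents (6 or more) and 0.1% with 232 (140 or more).

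**4. What volume would be enough?** Reusing the 60% threshold on the 180 target gives 108 recruits, or 36 per arm. At 42% loss, 36 × 0.58 = 20.9 respondents; at 60% retention, 36 × 0.60 = 21.6. Both fall well short of 35. Reaching 35 takes 35/0.58 = 60.3 recruits per arm at the assumed loss, or 35/0.60 = 58.3 at the retention threshold. A volume band copied from the consent percentages would not serve.

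**5. By arm.** Illustration with equal arms of 60: retention of 75%, 75% and 30% gives 45 + 45 + 18 = 108 of 180 = 60%, a *go* if judged overall, with 18 respondents in one arm. Requiring the lowest arm to pass has its own cost. With true consent of 65% in every arm and 77 screen-positive parents per arm (232/3), one arm falls below 60% with probability 0.197, so at least one does with probability 1 − (1 − 0.197)³ = 48%. Judged overall on 232, the chance of missing 60% is 6%. For retention at a true 65% with 60 per arm the figures are 43% and 7%. All of these assume independent parents; clustering by practitioner would change them.

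**The case against.** **A reader might infer that the *go* criterion cannot be met.** The documents do not support that. The Aim section compares the 60% with a consent rate of 80% in primary care trials and presents it as more cautious, and Sample size applies the 78% after the screening step. Both make sense only as consent among people who are asked, and only screen-positive parents are asked. The intended denominator is reasonably clear. What stands is that the text does not state it, and that three sections use the word for the wider set.

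**Low recruitment would be visible anyway.** The objectives include estimating eligibility and recruitment rates, Statistical analyses reports numbers recruited and retained, and the process evaluation looks at disclosure and barriers. That is a fair point about reporting. It does not change the rule, which calls meeting all of the listed targets a clear success, and none of those targets is a number of parents.

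**A reader might also infer that the protocol pools the arms for consent and retention.** It does not say so. Pooling is inferred because a per-arm condition is written for intervention receipt only, and by-arm reporting is something an article may leave to a fuller document. That practitioners know their allocation is likewise inferred, from arm-specific training and from delivery in the same contact as recruitment. The splits in step 5 are illustrations. A rule that the lowest arm decides is not called for either: it would miss *go* about half the time at a true 65% consent.

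**Conclusion.** The point holds as a defect in a stated decision rule.

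- **Denominator.** The wording conflicts with the protocol's own use of *eligible*. The same planned data give 23.4% (at most 30%) or 78%, on opposite sides of both thresholds. The 30% ceiling rests on the protocol's positivity assumption.
- **Volume.** On the intended reading no criterion depends on the number screened or recruited, so *go* is possible at about 10% of the 180 target and about 4 respondents per arm. That case assumes the planned 84%, 30% and 78% hold at one tenth of the screening, with retention and receipt just above 60%. It shows what the rule allows and is not a forecast.
- **Arms.** Differential recruitment by arm is a real risk in this design. It warrants by-arm reporting and consideration in the progression decision, not a stricter threshold.

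**What to change.** 1. State the consent denominator as parents who meet the inclusion criteria, score 5 or more on the AUDIT-C and are invited. Use it in both the *go* and the marginal band.
2. Add a recruitment-volume criterion with *go* and marginal bands. The team should set these against the 180 target and the 35 respondents per arm, bearing in mind that 108 recruits would not deliver 35 per arm. Report the proportion of eligible caseload parents who were screened, and the screen-positive rate.
3. Report screen-positive rate, consent, 12-month retention and baseline AUDIT-C by arm, and say that any imbalance will be considered in the progression decision. Do not make the lowest arm decisive.

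The Timescale section says recruitment is under way, so these changes should be settled and dated before the criteria are applied.

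Cost: a few sentences and a few tables. Practitioners already record the demographics of all eligible parents, so most of the data will exist. The downside is that a clear *go* becomes somewhat harder to reach.

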
### Randomisation and blinding

The study will employ a cluster randomisation design, with the practitioners being the unit of randomisation. As a single practitioner works with all family members, this will prevent within-family contamination (i.e. if multiple members of one family are recruited to the trial, all family members will receive the same intervention), as well as reducing contamination caused at a practitioner level. The intervention delivered by the early help family support and social care practitioners is provided to the participant immediately following recruited and within the same contact. As such, randomisation will not be compromised by a change in the participant’s allocated practitioner. The practitioners will be randomised to one of the three trial arms in a 1:1 ratio using block randomisation. The study statistician will allocate practitioners to trial arms using a randomised sequence created in Stata 14 [60]. The randomisation will be stratified by a local authority area and practitioner role (early help practitioner, family support worker, social worker within the assisted and support year in employment and progressed social worker), with equal probabilities for each of the three arms and randomly generated varying block size. Service level (early help family support or statutory children’s social care) should be balanced across the strata by the randomisation. Blinding of group allocation will not be possible for the participants or the researcher completing follow-up questionnaires. The study statistician and health economist will be blind to group allocation throughout analysis; participants and practitioners will only be identified by study numbers. Within a definitive trial, researchers, statisticians and health economists will be blinded.

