### Sample size

As this is a pilot feasibility trial and not an outcome evaluation, no formal power calculation is required [61]. Rather, the function of a pilot feasibility trial is to provide data that can inform a power calculation for a future definitive trial. For the pilot trial, a minimum of 35 respondents in each trial arm at the 12-month follow-up is required to estimate the critical parameters to the necessary degree of precision for a continuous primary outcome (number of occasions drinking 5+ standard drink units in a single occasion as derived from the TLFB/30) [62]. Attrition of 33% at the 12-month follow-up is generally assumed within feasibility trials [63]. However, due to a paucity of trial-based research conducted with parents involved in early help family support and children’s social care, a cautious 42% loss to follow-up has been applied. Consequently, the sample size to be recruited will be inflated to 60 parents in each of the three arms (Please see Fig. 1).

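### The 12-month retention target has no arm qualifier, so it can be passed when one of the three arms has kept fewer than half of its parents

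*Protocol article*

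**What the plan says.** The Aim section lists four targets, all of which must be met for a clear go: three local authorities, consent, attendance at the intervention, and 12-month retention.

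- **Retention, go:** at least "60% of consented participants for provision of key outcome data at 12 months".
- **Retention, marginal:** 50–59% "of consented participants at 12 months". Marginal results go to ADePT.
- **Receipt of intervention:** at least "60% of randomised participants in each arm receive the intervention". This is the only target set by arm.

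Under Sample size, "a minimum of 35 respondents in each trial arm at the 12-month follow-up is required" and "a cautious 42% loss to follow-up has been applied", which leads to 60 parents recruited per arm. Under Randomisation and blinding: "Blinding of group allocation will not be possible for the participants or the researcher completing follow-up questionnaires". The Discussion treats the choice between two and three arms as a key question for the definitive trial.

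**The concern.** The word pooled does not appear, but it is the plain reading of a percentage of consented participants with no mention of arm, next to a criterion that does name each arm. Read that way, the rule takes one input, the total retained over the total consented, and cannot tell 36/36/36 from 24/42/42.

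The arms ask different things of the parent: a leaflet, alcohol advice from the family's own practitioner, or that advice plus an invitation to an alcohol treatment service. Participants and the follow-up researcher know the allocation. The Discussion itself says that the practitioner relationship could feel threatening and that these drinkers may not see specialist services as meant for them. Loss that depends on arm is therefore plausible. In a definitive trial it would threaten the between-arm comparison, and it bears directly on how many arms to keep. As the rule stands, a pilot that showed it could still be recorded as a clear success on retention.

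**Working it through.** **Inputs from the protocol article.** 60 parents per arm in three arms, 42% loss, 35 respondents per arm (Sample size); go at 60%, marginal down to 50% (Aim).

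**The plan's own figure.** 35 / (1 − 0.42) = 60.3, against the stated 60. In reverse, 60 × 0.58 = 34.8, about 35. The sample size reproduces to within rounding. It also fits the 60% bar at trial level: 3 × 35 = 105 respondents, against 0.60 × 180 = 108.

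**What the bar admits.** Splits that total exactly 108 of 180:

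| Retained per arm | Percent per arm | Gap (points) |
|---|---|---|
| 36/36/36 | 60/60/60 | 0 |
| 28/40/40 | 47/67/67 | 20 |
| 24/42/42 | 40/70/70 | 30 |
| 20/44/44 | 33/73/73 | 40 |

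All four return the same answer. For an arm to be below 50% (29 of 60 or fewer) at the bar, the other two must together hold at least 108 − 29 = 79 of 120, or 65.8%. The gap therefore has to be large before the problem appears.

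**How often this could happen.** Let X1, X2, X3 be the numbers retained, taken as independent binomials with n = 60 and assumed true rates. Pass means X1 + X2 + X3 ≥ 108. Low arm means min(X1, X2, X3) < 30. Exact probabilities:

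| Assumed true retention | P(pass) | P(low arm given pass) | P(pass and no low arm) |
|---|---|---|---|
| 75/65/45% | 0.71 | 0.66 | 0.24 |
| 70/70/40% | 0.53 | 0.87 | 0.07 |
| 65/62/55% | 0.60 | 0.08 | 0.56 |
| 60/60/60% | 0.53 | 0.02 | 0.52 |

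The last column is the pass probability once a 50% floor per arm is added.

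**Clustering.** Simulation with 15 practitioners of 4 parents per arm and an assumed intracluster correlation of 0.05 changes little. At 75/65/45%, P(pass) is 0.70 and 64% of passes have a low arm. At equal 60%, about 3% of passes have a low arm.

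**The case against.** **There is no contradiction in the plan.** The 60% bar and the sample size agree, and the stated aim is whether these parents can be retained at all, which a trial-level figure answers. This stands: the point improves a decision rule and does not correct an error.

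**The receipt target is set by arm for a stated reason.** Receipt is expected to differ between opportunistic and scheduled sessions, whereas follow-up uses one procedure for everyone. This is fair, so the contrast between the two criteria supports the pooled reading but does not show an oversight. The receipt target still measures uptake and cannot detect loss to follow-up.

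**Imbalance would probably be noticed anyway.** The Economic evaluation section promises a look at possible bias in follow-up completion and tables most outcome data by arm, and the process evaluation samples by arm. This is likely true, but none of it enters the stop/go rule or triggers ADePT.

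**The large figures rest on assumed gaps of 20–30 points or more.** This is also correct; at 65/62/55% the problem is small.

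**A stronger reading that does not hold.** A reader might infer that the rule breaches the plan's own requirement of 35 respondents per arm. The documents do not support that. The 35 is a precision target for estimating parameters, not a progression threshold, and an arm at 33 or 34 loses a little precision without showing infeasibility. With equal true retention of 60%, about 49% of passes have some arm below 35, but that is chance around an expected 36 and is not evidence of differential attrition.

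**Conclusion.** The point holds as a weakness in a pre-specified rule. The retention criterion cannot see arm, no other target makes up for this, and a pilot with one arm at 40% and two at 70% would pass it without ADePT.

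How much this matters depends on how unequal retention is. About two thirds of passes hide an arm below 50% at an assumed 75/65/45%, and about one in twelve at 65/62/55%. These rates are assumptions. The figures also take 60 parents recruited in every arm, and they concern the retention criterion only, since an overall go needs the other three targets too.

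The conclusion does not extend to saying that the sample size is wrong or that the 35 per arm is a failed criterion. The change is worth making because it costs almost nothing.

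**What to change.** Keep the overall 60% bar and add one sentence to the stop/go criteria in the Aim section: *retention counts as go only if, in addition, no arm has 12-month retention below 50%; otherwise the result is treated as marginal and appraised under ADePT.* The 50% is the lower marginal limit already in the plan, so no new threshold is introduced.

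**Cost.** No new data. If true retention is 60% in every arm, about 2% of passes become marginal (about 3% with an intracluster correlation of 0.05); at 65% in every arm it is about 1%.

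**What it achieves.** P(pass) falls from 0.71 to 0.24 at 75/65/45% and from 0.53 to 0.07 at 70/70/40%.

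**What it does not do.** A floor of 30 of 60 does not secure 35 respondents per arm: at 75/65/45%, about 90% of the remaining passes still have an arm below 35. If the investigators want that number to bind, they would have to say so separately. Reporting retention by arm with an interval for the difference is ordinary content for the analysis plan and is not asked for here.
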